## Abstract

**Background:**

Hospital-acquired infections (HAIs) are significant public health issues, especially in low-and middle-income countries (LMICs). Hand hygiene and low-level disinfection of equipment practices among healthcare workers are some of the essential measures to reduce HAIs. Various infection prevention and control (IPC) interventions to reduce HAI incidence have been developed. However, effective interventions have not been well developed in the LMICs context. Therefore, this protocol aims to develop, pilot, and assess the feasibility and acceptability of an IPC intervention in Cambodia and the Lao People’s Democratic Republic.

**Methods:**

This study will consist of four phases guided by the Medical Research Council (MRC) Framework. Three hospitals will be purposely selected – each from the district, provincial, and national levels – in each country. The gap analysis will be conducted in Phase 1 to explore IPC practices among healthcare workers at each hospital through desk reviews, direct observation of hand hygiene and low-level disinfection of equipment practices, in-depth interviews with healthcare workers, and key informant interviews with stakeholders. In Phase 2, an IPC intervention will be developed based on the results of Phase 1 and interventions selected from a systematic literature review of IPC interventions in LMICs. In Phase 3, the developed intervention will be piloted in the hospitals chosen in Phase 1. In Phase 4, the feasibility and acceptability of the developed intervention will be assessed among healthcare workers and representatives at the selected hospitals. National consultative workshops in both countries will be conducted to validate the developed intervention with the national technical working groups.

**Discussion:**

The MRC Framework will be employed to develop and evaluate an intervention to reduce HAIs in two LMICs. This theoretical framework will be used to explore the factors influencing hand hygiene compliance among healthcare workers. The gap analysis results will allow us to develop a comprehensive IPC intervention to reduce HAI incidence in Cambodia and Lao People’s Democratic Republic. Findings from this protocol will feed into promising IPC interventions to reduce HAI incidence in other resource-limited settings.

**Clinical trial registration:**

ClinicalTrial.Gov, identifier NCT05547373.

## Introduction

Infection prevention and control (IPC) has been recognized as a vital component in health systems as it affects patients and healthcare workers (1). Inadequate adherence to the standard protocols of IPC results in hospital-acquired infections (HAIs) that often occur in patients in medical care (2). HAIs have received little public health attention, particularly among policymakers in low-and middle-income countries (LMICs) (3). As a result, millions of patients are affected by HAIs each year globally. A wide gap exists between countries in the HAI prevalence, varying between 3.5–12% in high-income countries and 5.7–19.1% in LMICs at any given time. WHO further recognizes a lack of evidence on IPC in LMICs, suggesting that more research in these countries is warranted.

The recent coronavirus disease 2019 (COVID-19) pandemic has proven the significance of IPC in saving lives by reducing HAIs. The stringent and enhanced IPC measures introduced at various hospitals to fight against the pandemic have reduced HAI incidence markedly (4–8). However, the prevalence of HAIs could be extremely high in LMICs. For instance, the HAI prevalence among adults in intensive care units in Vietnam was estimated to be 29.5% in 2015 (9). Regarding the economic burden of HAIs in LMICs, available United States and Europe data suggest that HAIs cost several billion dollars annually (10). It has been estimated that the five significant HAIs – central line-associated bloodstream infections, ventilator-associated pneumonia, surgical site infections, *clostridium difficile* infections, and catheter-associated urinary tract infection – cost the United States approximately USD 9.8 billion annually (11). Evidence of mortality and increased antibiotic resistance due to HAIs have also been documented (12, 13).

Against this backdrop, several IPC interventions to reduce HAIs have been developed, implemented, and evaluated worldwide (14). In magnet-designated hospitals in California, the United States, effective and adequate implementation of IPC programs, including healthcare workers’ adherence to hand hygiene guidelines, routine fomite disinfection, environmental decontamination, and antimicrobial stewardship programs, have significantly contributed to reducing the HAI incidence (15). A recent study revealed that interventions on structural inputs (e.g., availability of hand sanitizers), standard care processes, and their combination reduced HAI incidence significantly (14). Additionally, the review highlighted promising interventions, including using disinfection technology, such as ultraviolet light and hydrogen peroxide vapor, while noting that many existing studies lack rigor in their design and methods.

Hand hygiene is one of the simplest and most effective measures for preventing HAIs. Hand hygiene prevents patient infections, the hospital environment contamination with pathogens, and the cross-transmission of microorganisms between patients (16). Despite the effectiveness, a study on IPC practices in Cambodia identified barriers to promoting hand hygiene, including inadequate environmental hygiene, insufficient protective equipment, understaffing, overcrowding, and poor knowledge of infection control measures among healthcare workers and caregivers (17). Inadequate staff capacity and commitment, limited support from decision-makers, and financial shortages for IPC implementation have also been iterated (18).

Disinfection of reusable medical devices is another critical component of IPC interventions. Medical equipment that comes into physical contact with patients and healthcare workers is susceptible to colonized pathogenic microorganisms (19). For instance, a study found that stethoscopes and sphygmomanometers were associated with HAIs due to their contamination with bacteria (20). Disinfection of the equipment removes the microorganisms, preventing the transmission of organisms between patients (21). Guidelines for reusable equipment, environmental cleaning, and disinfection are included in the IPC national guidelines in Cambodia and Lao People’s Democratic Republic (22, 23) and WHO’s guidelines on core components of IPC programs at the national and acute healthcare facility levels (2).

Cambodia and Lao People’s Democratic Republic have been striving to tackle HAIs despite inadequate IPC infrastructures, a lack of IPC support services and surveillance and reporting systems for HAI incidence, limited IPC implementation capacity, and financial constraints (24, 25). Moreover, data on HAI prevalence and IPC-related knowledge, attitude, and practice among healthcare workers in LMICs are scarce. Such a paucity of data further prevents researchers from estimating the burden of the HAI endemic and devising proper IPC interventions to reduce HAI incidence.

The national guidelines and training curriculums have been distributed to the subnational levels in Cambodia and Lao People’s Democratic Republic. However, the evaluation mechanisms for IPC implementations and HAI surveillance systems have not been formalized. Based on anecdotal evidence in Cambodia, there has been a strong emphasis on the need for behavioral change among healthcare workers in adhering to the national IPC guidelines and evidence-based research, which is imperative for addressing this challenge. Although it lacks rigor in the methods, a study of hand hygiene education among healthcare workers in a provincial referral hospital in Cambodia showed that hand hygiene education using the WHO Guidelines on Hand Hygiene (26) reduced surgical site infections significantly (24). Therefore, documenting gaps in IPC implementation and practices in the local context to identify the appropriate and feasible IPC intervention components related to behavioral factors is a critical first step to reducing HAIs using evidence-based interventions.

Designing an effective IPC intervention involves several components and varies across healthcare settings. The Medical Research Council (MRC) Framework for Developing and Evaluating Complex Interventions has been employed across many disciplines (27–30). According to this framework (31, 32), the first step in developing a complex intervention is to identify the burden of the problems and the limitations of the current implementations and practices (32). The second step involves identifying the existing interventions. The third step is to develop a theoretical intervention model based on the gap in implementation and practices and the current evidence on effective interventions. Once the intervention is developed, a pilot study and the feasibility and acceptability assessment of the piloted intervention are required.

Based on this framework, this protocol aims to develop, pilot, and assess the feasibility and acceptability of an IPC intervention in Cambodia and Lao People’s Democratic Republic. The protocol’s specific objectives are to (1) conduct a gap analysis of IPC implementation and practices among healthcare workers at district, provincial, and national hospitals to identify IPC intervention components, (2) develop an IPC intervention based on the gap analysis findings and model interventions from a systematic review of IPC interventions to reduce the HAI incidence in LMICs, and (3) pilot the IPC intervention and assess its feasibility and acceptability among healthcare workers and stakeholders in Cambodia and Lao People’s Democratic Republic.

## Methods and analysis

### Study settings and design

The healthcare systems in Cambodia and Lao People’s Democratic Republic are organized into distinct levels, encompassing the district, provincial, and national tiers (33, 34). This study will be conducted in three hospitals in each country, with each hospital purposively selected from each healthcare system level (national, provincial, and district levels). One national hospital will be selected from the country’s capital city. Then, one province will be selected, and the provincial hospital and one district referral hospital will be selected. The intensive care unit, surgery unit, and medical ward will be selected for national and provincial hospitals, and the surgery unit, maternal and child health ward, and medical ward will be selected for district hospitals.

The study will be conducted between January 2023 and December 2024. As shown in Figure 1, the IPC intervention development will involve four phases: (1) gap analysis, (2) intervention development, (3) pilot implementation of the developed intervention, and (4) feasibility and acceptability assessment of the pilot implementation (32, 35).

**Figure 1 fig1:**
[figure not shown]
Project milestones and timelines.

#### Phase 1: Gap analyses

The gap analysis aims to identify gaps in the implementation and practices of hand hygiene and low-level disinfection of equipment guidelines among healthcare workers in the selected hospitals in each country. The gap analysis will involve a desk review of IPC national policies and guidelines, key informant interviews (KIIs) with key stakeholders, in-depth interviews (IDIs) with healthcare workers, and direct hand hygiene and low-level disinfection of equipment practice observations among healthcare workers in the selected hospitals.

Firstly, the “National Guidelines for Infection Prevention and Control in Healthcare Facilities” in Cambodia and Lao People’s Democratic Republic (22, 23) will be reviewed to assess if these guidelines are aligned with the WHO’s “Guidelines on Core Components of Infection Prevention and Control Programs at the National and Acute Health Care Facility Level” (2). Additionally, the policies and guidelines regarding IPC practices during the COVID-19 pandemic will be reviewed.

Secondly, the perspective of key stakeholders from each country on the gaps in IPC implementation and practices among healthcare workers will be explored by conducting KIIs. Three national stakeholders from each country will be recruited. In Cambodia, the national stakeholders will be the representatives of MoH’s Communicable Disease Control Department and the Department of Hospital Services and the selected national hospital. In Lao People’s Democratic Republic, stakeholders will be representatives of the MoH’s Department of Health Care and Rehabilitation, Communicable Disease Control Department, and the selected national hospital. At the provincial level, one representative of the provincial health department and one representative of the selected provincial hospital will be purpovely selected. Finally, two district key stakeholders will be purposely selected – one from the operational district office and one from the selected district hospital. A representative from the WHO for the KII from each country will also be included.

For IDIs, three healthcare workers (a doctor, a midwife, and a nurse) will be selected from each selected hospital ward, totaling 27 healthcare workers per country (Table 1). In addition, direct observations of hand hygiene and low-level disinfection of equipment practices will be conducted concurrently with the IDIs and KIIs at the selected hospitals, targeting doctors, nurses, and midwives. Eligible participants will include healthcare workers who (i) are aged 18 years or older, (ii) have worked in the selected wards of the chosen hospitals for at least 6 months, and (iii) who will be able to and agree to provide informed consent to participate in the study. Interns and visiting healthcare workers will be excluded.

**Table 1 tab1:** Sample size across the three hospitals in each country (Cambodia and Lao People’s Democratic Republic).

Health system level	Number of hospitals^a^	Number of IDI participants	Number of KII participants	Total
World Health Organization			1	1
National	1	9	3	12
Provincial	1	9	2	11
District	1	9	2	11
Total	3	27	8	35

IDI, in-depth interview; KII, key-informant interview.

a For the national and provincial hospitals, we will select intensive care units, surgery units, and medical wards. We will select surgery units, maternal and child health wards, and medical wards for district hospitals.

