### Tool development

#### For gap analyses

A standardized WHO’s hand-hygiene observation tool for direct observation (Supplementary material 1) will be adapted for this study (39). The observation form contains two main elements: a header and an observation grid. The header will enable the observers to record the time, date, and location of the selected wards. The observation grid allows observers to record the data to compute the hand hygiene compliance of the healthcare workers.

An observation form will be adapted from an existing study (Supplementary material 2) (40) to observe the low-level disinfection of equipment compliance among healthcare workers. Low-level disinfectants are used to disinfect noncritical items that come into contact with skin. According to the national guidelines on IPC for healthcare facilities, the equipment includes bedpans, toilets, urinals, blood pressure cuffs, electrocardiogram leads, thermometers, stethoscopes, beds, and bedside tables (22, 23).

In Phase 1, IDIs using an interview guide (Supplementary material 3) with healthcare workers will be conducted to understand the factors influencing their hand-hygiene practices. A topic guide from an existing study (41) will be adapted, containing questions derived from 14 theoretical domains to capture multiple-level determinants of health-related behavioral change. Furthermore, healthcare workers will be asked how the COVID-19 pandemic has impacted their hand-hygiene practices.

Additionally, A KII topic guide (Supplementary material 4) will be developed to understand the perspective of key stakeholders about the gap in IPC implementation and practices among healthcare workers in both countries, adapting questions from an existing study (42). Questions on the impact of the COVID-19 pandemic on HAI prevention and control in each country will also be included in the interview guide.

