### Training and data collection procedures

Before the data collection in Phases 1 and 4, the study coordinators will train data collectors in a two-day workshop, followed by another day for study tool pretesting. Data collectors will include staff and graduate students from the University of Health Sciences (UHS) in Cambodia and the Lao Tropical and Public Health Institute (Lao-TPHI) in Lao People’s Democratic Republic. The training will cover direct observations and interview techniques, including confidentiality, privacy, and data quality control.

For hand-hygiene observation, training materials will be adapted from WHO’s training tools (45). The adapted training materials will include PowerPoint presentations and an educational video of healthcare workers performing care in hospital settings. The training will include observation of healthcare workers’ hand-hygiene practices at the selected hospitals. Each observation session will last approximately 20 min (+10 min buffer time, depending on the observed activity) (26). The WHO’s five moments of hand hygiene will be applied: (1) before touching patients or patient surroundings, (2) before a clean/aseptic procedure, (3) after body fluid exposure risk, (4) after touching a patient, and (5) after touching the patient’s surroundings (26). The hand-hygiene actions will be recorded when either handwashing with soap and water or alcohol hand rubbing is observed according to the five moments indicated above. To obtain reliable estimates of the compliance rate, WHO recommends at least 200 opportunities for each ward per observation period (26). The observations will be conducted during the regular working hours of 8: 00 AM–12: 00 PM and 1: 00 PM–5:00 PM.

Similarly, observers will be trained to observe practices among healthcare providers. Healthcare providers will be considered practicing low-level disinfection of equipment if they disinfect non-critical medical equipment (i.e., bedpans, electrocardiogram leads, stethoscopes, blood pressure apparatus, thermometers, pulse oximeters, glucometers, beds, and bedside tables) with approved disinfectants before and after the equipment comes to contact with patients.

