Study coordinators will also train data collectors on qualitative data collection techniques using interview guides for IDIs and KIIs. In Phase 1, the IDIs questions will be guided by the TDF (46) to assess factors influencing healthcare workers’ hand-hygiene practices. However, rigidly applying the TDF may result in specific determinants or gaps being overlooked. Therefore, the interviewers will be instructed to be open to any responses from the participants so that the responses will be distinct from the pre-determined TDF domains. Moreover, the interviewers will be trained to use simple languages so that the participants can comprehend the questions correctly.

The hand hygiene and low-level disinfection of equipment observation training in Phase 4 will include the same contents as in Phase 1. Additionally, the study coordinators will train interviewers on conducting IDIs and KIIs, including using neutral wording and probing questions.

Following the training in Phases 1 and 4, the interviewers and observers will spend one morning pretesting the topic guides for IDIs and KIIs and the observation form on hand hygiene and low-level disinfection of equipment in one hospital in the capital city of each country. In the afternoon, all the interviewers and observers will reflect on their experience with the study tools and provide feedback.

Potential participants from each selected hospital will be invited through the heads of the selected hospitals and wards and asked them for signed informed consent. Each interview will take approximately 45–60 min to complete. The interviews will be audiotaped, and notes will be taken during the interviews with the participants’ permission. The samples and sampling procedures will be similar in Cambodia and Lao People’s Democratic Republic.

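### Phase 1 observation overlaps with staff interviews on hand hygiene and follows practice observation at the study hospitals, so baseline hand-hygiene compliance may be raised

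*Protocol article*

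**What the plan says.** **Timing.** The Phase 1 section of the protocol article states that "direct observations of hand hygiene and low-level disinfection of equipment practices will be conducted concurrently with the IDIs and KIIs at the selected hospitals". The same section adds that "three healthcare workers (a doctor, a midwife, and a nurse) will be selected from each selected hospital ward, totaling 27 healthcare workers per country".

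**Subject of the interviews.** Under Tool development (For gap analyses), the in-depth interviews with ward staff "will be conducted to understand the factors influencing their hand-hygiene practices". The key informant interviews are broader and ask "about the gap in IPC implementation and practices among healthcare workers in both countries". Each interview takes 45 to 60 minutes.

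**Observer training.** Under Training and data collection procedures: "Before the data collection in Phases 1 and 4, the study coordinators will train data collectors in a two-day workshop". Of hand hygiene it says: "The training will include observation of healthcare workers’ hand-hygiene practices at the selected hospitals". The tools are then pretested "in one hospital in the capital city of each country".

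**Phase 4.** Observation and both kinds of interview are repeated. Table 3 gives 36 interviewed healthcare workers per country, and the observation training has the same contents as in Phase 1. The order of observation and interviews is not given.

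**Use of the baseline.** Phase 1 is meant to identify gaps in practice, and it feeds the development of the intervention. Its compliance rates are also compared with those of Phase 4 by t-test, and no control group is described. The Discussion acknowledges the Hawthorne effect and argues that it fades because each ward is observed for 14 days.

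**The concern.** A worker who spends up to an hour explaining what helps or hinders their hand hygiene has been reminded of it, and may discuss it with colleagues. If this happens while the ward's compliance is being recorded, some recorded opportunities come from prompted staff. Practice observation at the study hospitals before data collection may act the same way.

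The main stake is the gap analysis. It should describe usual practice, and a raised rate makes the gap look smaller. Nothing done in Phase 4 can repair that.

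The second stake is the before–after comparison. With no control group, a change in measurement conditions between phases cannot be separated from the effect of the intervention.

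The 14-day argument relies on staff getting used to the observer. Interviews on the same behaviour during those days work against that, and the limitations paragraph mentions neither interviews nor training visits.

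**Working it through.** **1. The plan's own figure.** 3 workers × 3 wards × 3 hospitals = 27 interviewed healthcare workers per country, as stated. Every observed ward therefore supplies three interviewees.

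**2. What the documents cannot give.** They contain no data on how far an interview changes behaviour, no expected compliance rate and no headcount of observed staff. The size of any rise cannot be computed. Steps 3 to 5 are a sketch on these assumptions:
- observed staff per ward equal the Phase 3 pilot numbers in Table 2 (15 national, 10 provincial, 7 district; 96 per country), a proxy only;
- each worker contributes equally many opportunities;
- an interview raises that worker's compliance by d = 5, 10 or 20 points, with no spill-over to colleagues.

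**3. Share of observed staff interviewed in Phase 1.** National 3/15 = 20%; provincial 3/10 = 30%; district 3/7 = 43%; country 27/96 = 28.1%.

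**4. Gross shift in the Phase 1 country rate.** Shift = share × d if all interviews come first, and half of that if they are spread evenly over the observation window. Concurrent conduct is closer to the second.

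| d (points) | All interviews first | Spread evenly |
|---|---|---|
| 5 | 0.281 × 5 = 1.4 | 0.7 |
| 10 | 0.281 × 10 = 2.8 | 1.4 |
| 20 | 0.281 × 20 = 5.6 | 2.8 |

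**5. Net effect on Phase 4 minus Phase 1.** The Phase 4 share is 36/96 = 37.5%. If the same reaction occurs in both phases, net = (0.375 − 0.281) × d. If Phase 4 observation is finished before its interviews, net = −0.281 × d. Values for even spreading are in brackets.

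| d (points) | Reaction in both phases | Reaction in Phase 1 only |
|---|---|---|
| 5 | +0.5 (+0.2) | −1.4 (−0.7) |
| 10 | +0.9 (+0.5) | −2.8 (−1.4) |
| 20 | +1.9 (+0.9) | −5.6 (−2.8) |

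A positive value overstates the change and a negative one understates it. The sign depends on the Phase 4 order, which is not stated.

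**6. By hospital level.** Phase 4 interviews average 15/3 = 5, 12/3 = 4 and 9/3 = 3 workers per ward, against 3 in Phase 1. With d = 10, the reaction in both phases and all interviews first, the net effect is (5 − 3)/15 × 10 = 1.3 points (national), (4 − 3)/10 × 10 = 1.0 (provincial) and (3 − 3)/7 × 10 = 0 (district). The district wards have the largest gross shift and a net effect of zero.

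**7. Which behaviour is affected.** The ward-staff interviews and the training observation at the selected hospitals are both described for hand hygiene only. The key informant interviews cover infection control generally, but only three of the eight per country are with hospital representatives, who are not said to be observed ward staff. The case for equipment disinfection is therefore weaker.

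**The case against.** The other side has several good points.

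- **Phase 4 is similar.** It repeats the interviews, the forms and the observation training, so part of any reaction may cancel. This stands for the comparison. It does not help the gap analysis, which uses Phase 1 alone.
- **Observation is open anyway.** Staff consent and are watched for 14 days, and reactivity is a listed limitation. This also stands: re-ordering removes only the avoidable part and will not produce a pure usual-practice baseline.
- **The training sentence is ambiguous.** It could describe what is taught, and the only field session given a time is the pretest morning. Practice at the study hospitals is the more natural reading, but the article gives no duration and names no wards.
- **Sequencing is detail for the full protocol.** This would hold if the article were silent. It states concurrent conduct as a rule.

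Two stronger readings are tempting. From the location of the pretest, a reader might infer that the national study hospital is exposed a further time. That hospital is in the capital, but the article does not say that it is the pretest hospital. A reader might also take an assumed rise of 10 to 15 points in 3 of 7 to 15 staff and infer a bias of 2 to 6 points (3/15 × 10 = 2.0; 3/7 × 15 = 6.4). That would be a gross Phase 1 shift with every interview held first, on an assumed rise and proxy headcounts. It is not the bias in the comparison.

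**Conclusion.** The point holds for hand hygiene as a possible and avoidable bias. The article fixes concurrent observation and interviewing on the same behaviour, and most naturally reads as placing practice observation at the study hospitals beforehand. Observed Phase 1 compliance may be raised, so the gap analysis may understate the gap. The 14-day argument does not answer this.

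The documents do not show that the baseline is in fact raised, nor that the before–after difference is biased in a particular direction. The size is unknown. The gross shift of 0.7 to 5.6 points in the country rate rests wholly on the assumed rise of 5 to 20 points and on pilot numbers used as headcounts. The net effect on the comparison could be small, cancel or go either way. This is a cheap improvement to the design and does not invalidate the study.

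**What to change.** 1. In both phases, complete observation on all selected wards of a hospital before the first in-depth interview or hospital-representative interview there, and state this order for Phase 1 and Phase 4.
2. Hold the observers' practice observation outside the study wards, preferably in a hospital that is not in the study.
3. Confirm that the capital-city pretest hospital is not the national study hospital.
4. If the order cannot be changed, use the same order in both phases and add interviews and training visits to the reactivity limitation in the Discussion.

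**Cost.** No participants are added. Interviews start about two weeks later at each hospital if its three wards are observed in parallel, and up to 3 × 14 = 42 days later if they are observed in sequence. The article does not say which applies.
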